##### Functional disability assessed using the ODI

2.5.2.2

The ODI is a standardized, self-reported questionnaire designed to assess functional disability related to LBP. It comprises 10 items, and the final score is expressed as a percentage ranging from 0 to 100%, with higher scores indicating greater disability. In this study, the baseline ODI score will be used as a descriptive measure of the participants’ functional limitations (19).

##### Patient-reported percentage pain reduction, PRPPR

2.5.2.3

PRPPR is a subjective metric in which participants rate their pre-procedure pain intensity as 100%, then report the percentage by which their pain has decreased after the procedure on a 0–100% scale. In pain intervention research, it has been suggested that evaluating the perceived percentage reduction—not just the absolute numerical change (e.g., NRS difference)—may provide a more sensitive measure of clinical improvement, especially when assessing early or immediate treatment response (20–22). Based on this rationale, PRPPR was selected as a secondary outcome measure in this study to capture the immediate analgesic effect following a single session of ultrasound-guided pharmacopuncture.

As this study is a prospective, comparative, observational trial conducted in a real-world clinical setting, complete assessor blinding based on needle type (Short vs. Long) is not feasible. Therefore, outcome assessors will evaluate participants in an unblinded state, with access to group allocation information.

Although this approach may introduce potential measurement bias, several strategies have been implemented to minimize its impact. All participating centers will adhere to a standardized assessment protocol, and outcome assessors will receive uniform training prior to the study’s initiation. Furthermore, all outcome measures—including NRS, ROM, ODI, and PRPPR—will be recorded consistently according to predefined operational definitions.

Despite these procedures, residual bias inherent in non-blinded assessments cannot be entirely eliminated. This limitation should be considered when interpreting the study findings.

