*If the subject is deemed eligible after screening, the first intervention will be performed immediately after obtaining informed consent. ^†^A telephone-based follow-up will be conducted within 1 day (24–36 h) after Visit 1. ^‡^D indicates “Day.” ^a^Demographic survey: information on gender, age, year of birth, height, weight, and other baseline characteristics will be collected. ^b^Medical history: includes previous history of low back pain(LBP), hypertension, diabetes, osteoarthritis, sleep disorders, psychiatric history, current medications, smoking history, and alcohol consumption. ^c^ODI (Oswestry disability index): the ODI is a validated questionnaire assessing functional disability related to LBP. It consists of 10 items covering pain intensity and daily activities, and yields a score ranging from 0 to 100%, with higher scores indicating greater disability. In this study, ODI is administered only at baseline to evaluate initial functional status. ^d^NRS (numeric rating scale): pain intensity for LBP will be assessed on a 0–10 scale, where higher scores indicate more severe pain. ^e^PRPPR (patient-reported percentage pain reduction): subjects will be asked to report the perceived percentage of pain reduction compared with pre-intervention status, on a 0–100% scale, both immediately after treatment and at Day 1 follow-up. ^f^ROM (range of motion): lumbar ROM—including flexion, extension, lateral flexion, and rotation—will be assessed to evaluate functional changes. ^g^Adverse events: adverse events or unexpected symptoms occurring immediately after the procedure or during follow-up will be assessed and recorded.

The study protocol has been submitted for Institutional Review Board (IRB) approval. Ethical approval will be obtained prior to the initiation of participant enrollment. No participants have been recruited or exposed to the intervention at the time of manuscript submission.

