#### Primary outcome

2.5.1

The primary outcome of this study is the change in Numeric Rating Scale (NRS) scores for LBP immediately following ultrasound-guided pharmacopuncture.

The NRS score recorded immediately before the procedure will serve as the baseline, and a second NRS assessment will be conducted immediately after the intervention (QPI-guided PDRN pharmacopuncture). The difference between the baseline and post-procedure scores will be calculated to determine the extent of symptom improvement. A between-group comparison of NRS changes (SNG versus LNG) will be used to evaluate whether needle length influences the magnitude of acute pain reduction.

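### Section 2.5.2.3 moves from incomplete blinding to fully unblinded assessment of the patient-rated primary NRS, without a safeguard that limits an assessor's influence on the score

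*Protocol article*

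**What the plan says.** Section 2.5.1 defines the endpoint: "The primary outcome of this study is the change in Numeric Rating Scale (NRS) scores for LBP immediately following ultrasound-guided pharmacopuncture". The baseline score is taken just before the procedure, and "a second NRS assessment will be conducted immediately after the intervention".

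Blinding is dealt with in section 2.5.2.3, after the PRPPR definition. The reason given is that "complete assessor blinding based on needle type (Short vs. Long) is not feasible" in a real-world observational setting. The conclusion drawn is that "outcome assessors will evaluate participants in an unblinded state, with access to group allocation information".

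The safeguards follow: "All participating centers will adhere to a standardized assessment protocol, and outcome assessors will receive uniform training prior to the study’s initiation", and "all outcome measures—including NRS, ROM, ODI, and PRPPR—will be recorded consistently according to predefined operational definitions". The section then concedes that "residual bias inherent in non-blinded assessments cannot be entirely eliminated" and asks readers to allow for this when interpreting the findings.

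On how the NRS is obtained, the footnote to Table 1 says only that "pain intensity for LBP will be assessed on a 0–10 scale, where higher scores indicate more severe pain". Section 2.1 adds that NRS and PRPPR are rated again straight after the injection, and that both are collected by telephone at 24–36 h. It also fixes the grouping by clinic: two sites contribute only short-needle cases and two only long-needle cases.

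**The concern.** That complete blinding is unattainable is a reason to accept partial protection. It is not a reason to give assessors the group for every measure. The distinction matters most for NRS and PRPPR. Both are the patient's own judgement, so nobody who knows the needle has to stand between the patient and the number. ROM is different, because someone must hold and read the goniometer.

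The safeguards standardise how a score is defined and recorded. A trained assessor following a common protocol can still influence an answer given minutes after an injection, through the wording of the question, tone or a follow-up prompt.

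At stake is the primary comparison. Each clinic contributes one needle length, so any difference between the two pairs of clinics in how ratings are elicited adds to the needle-length contrast, and no analysis can separate the two.

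**Working it through.** **1. The logic of section 2.5.2.3**

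| Step | What the section supports |
|---|---|
| Premise | Complete blinding of assessors to needle type is not feasible |
| Conclusion | Assessors work with group information, for NRS, ROM, ODI and PRPPR alike |
| Safeguards | Common protocol, uniform training, operational definitions |
| Not listed | Any step that separates the patient's rating from a person who knows the group |

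The premise excludes one option, full masking. It leaves lesser protections open, and the section does not consider them for the patient-rated measures.

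**2. The plan's own sample size (section 2.6.1)**

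Inputs: d = 0.56, two-sided alpha 0.05, power 80%, two-sample t-test, 1:1. The noncentral t solution is 51.03 per group, which rounds up to 52, or 104 in total. This matches the plan. Power is 80.7% at 52 per group and 86.0% at the target of 60 per group. The fix does not alter these figures.

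**3. Implied SD**

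The article gives mean reductions of 2.74 and 1.76 points, a difference of 0.98, which it rounds to about 1.0.

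- SD = 0.98 / 0.56 = 1.75
- SD = 1.0 / 0.56 = 1.79

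**4. What a spurious shift would do (illustration only)**

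Assume no true needle effect and a reporting shift of b points between the groups. The documents give no value for b, so a range is shown. The standardised shift is b / SD, and the noncentrality is (b / SD) × √(n/2) with n = 60 per group, so √30 = 5.477. For b = 0.5 and SD 1.75 this is 0.286 × 5.477 = 1.565, and the two-sided t-test at 0.05 rejects with probability 0.342.

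| Assumed shift b (points) | SD 1.75 | SD 1.79 |
|---|---|---|
| 0.1 | 6% | 6% |
| 0.25 | 12% | 12% |
| 0.3 | 15% | 15% |
| 0.5 | 34% | 33% |
| 1.0 | 87% | 86% |

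A shift of a quarter to a half of the planned 1-point difference would therefore raise the false-positive rate from 5% to about 12–34%. The table shows sensitivity to a bias if one exists. It is not evidence that one of this size exists here.

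**5. How much self-marking would remove**

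This cannot be derived. If the shift were 0.5 points (SD 1.75) and self-marking removed 25%, 50% or 75% of it, the rejection rate would fall from 34% to 21%, 12% or 7%. The documents do not favour any of these fractions.

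**The case against.** The strongest reply is that nothing is hidden. Section 2.5.2.3 names the measurement bias, lists safeguards and tells the reader to allow for what remains. That is true, and it means the point is neither a contradiction nor an error of calculation. But disclosure does not reduce bias in the primary outcome when a simple protection is available and unused.

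A second reply is that the article never says how the NRS is obtained. The patient may already mark it, with staff only transcribing it, and an article may leave such detail to the full protocol or case report form. This stands in part: a reader might infer that assessors ask for the score aloud, and the text does not establish that. What the text does state is that assessors evaluate participants with access to the group, and that the NRS is among the measures covered. If scores are already self-marked, one sentence saying so closes the point.

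A third reply is that the remedy reaches only part of the problem. This stands. Enthusiasm conveyed before or during the injection would still affect a self-marked score, needle length remains confounded with clinic, and ROM still needs an examiner. The telephone ratings cannot use a written form.

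Finally, only influence that differs between the two pairs of clinics biases the contrast. Section 2.1 says all four clinics routinely use both needles, so the documents do not show that staff favour the needle their clinic contributes.

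**Conclusion.** The point holds in a limited form. Section 2.5.2.3 treats the infeasibility of complete blinding as grounds for unblinded assessment of everything, including a primary outcome that the patient can record alone, and its safeguards do not limit an informed assessor's influence on that rating. The change is worth making before recruitment; section 2.1 states that nobody had been recruited when the manuscript was submitted.

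The size of the bias is unknown. The 12–34% range rests on an assumed shift of 0.25–0.5 points, no true effect, an SD of 1.75–1.79 carried over from a chronic low back pain trial, and 60 per group.

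Two stronger readings are not supported. One is that self-completed scores would remove much of the bias: no figure in the documents bears on that share, and patient expectation, operator expectation and site confounding all remain. The other is that the needle should be concealed from patients and group labels removed from the assessment sheets. Concealment sits uneasily with the statement in section 2.1 that standard patient care is not modified, and removing labels achieves little where the clinic itself identifies the group.

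**What to change.** - In sections 2.5.1 and 2.5.2.3, state how the NRS and PRPPR are obtained. Specify that the patient marks the immediate pre- and post-procedure NRS, and the immediate PRPPR, on a form before the operator or assessor asks for or sees the score.
- For the 24–36 h telephone NRS and PRPPR, use fixed, neutral question wording that is the same at all four clinics.
- Keep the limitation statement in section 2.5.2.3. It still applies to ROM, to patient and operator expectation, and to needle length being confounded with clinic. Describe self-marking as reducing interviewer influence, without stating by how much.

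The cost is a one-page form, a short instruction to assessors and probably a few incomplete forms. No additional assessor should be needed, and the sample size is unchanged.

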### Sample size and statistical analysis

2.6

#### Sample size calculation

2.6.1

Since no prior study has been conducted under conditions identical to the present trial, the effect size for this study was estimated based on comparable interventions and studies reporting changes in NRS or VAS as primary outcomes. In a double-blind randomized controlled trial evaluating pharmacopuncture in patients with chronic LBP, the mean reduction in pain after 3 weeks was 2.74 points in the treatment group and 1.76 points in the control group, yielding an estimated between-group difference of approximately 1.0 point and a Cohen’s d of approximately 0.56 (23). Similarly, a systematic review of acupuncture for acute LBP reported a mean difference of −1.75 points on the VAS compared with controls (95% CI: −2.39 to −1.12) (24), indicating a meaningful short-term analgesic benefit. Additionally, a single-arm study conducted in Japan evaluating ultrasound-guided hydrodissection demonstrated a reduction of more than 4 points on the VAS immediately after the procedure (25), suggesting that ultrasound-guided interventions may provide rapid short-term pain relief.

Additionally, although the Minimum Clinically Important Change (MCIC) for acute LBP has been reported to be approximately 3.5 points on the NRS scale (26), such thresholds primarily apply to single-arm studies evaluating absolute symptom improvement. In comparative trial designs, such as the present study, the full magnitude of the MCIC is not required to determine a meaningful treatment difference. Instead, between-group differences of approximately 1 point—similar to those reported in previous randomized controlled trials—may still represent a clinically relevant effect when assessing comparative therapeutic outcomes.

Based on the literature reviewed, the effect size for this study was set at Cohen’s d = 0.56. Using a two-sample *t*-test with a significance level of 0.05 and a statistical power of 80%, the minimum required sample size was calculated to be 104 participants (52 per group). Allowing for an anticipated dropout rate of approximately 10%, the final target sample size was set at 120 participants, with 60 allocated to the short-needle group and 60 to the long-needle group.

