**Figure 2 fig2:**
[figure not shown]
Comparison of the two magnetized needle types used in this study (26G × 60 mm and 25G × 100 mm).

All four participating clinical sites routinely use both types of needles in daily practice, depending on actual clinical circumstances. For the purpose of comparative analysis, two sites will be designated to contribute only cases treated with short needles, while the other two sites will contribute only cases treated with long needles. This approach represents a site-level data extraction scheme, rather than a randomized allocation process, and is designed to enable comparative analysis of procedures performed in routine clinical practice without modification of standard patient care.

The study procedures consist of three stages: screening, the treatment visit (Visit 1), and post-procedure follow-up at 24 to 36 h. After providing written informed consent, participants undergo screening, during which demographic characteristics and relevant medical history are collected, and eligibility is assessed based on predefined inclusion and exclusion criteria. Participants who meet all eligibility criteria proceed directly to Visit 1, during which the ultrasound-guided pharmacopuncture intervention and all corresponding study assessments are conducted.

During Visit 1, all enrolled participants undergo a single ultrasound-guided PDRN pharmacopuncture procedure following a standardized protocol. Prior to the intervention, baseline assessments are conducted, including Numerical Rating Scale (NRS) scores for LBP and radiating leg pain, lumbar ROM, the Oswestry Disability Index (ODI), and the Patient-reported Percentage Pain Reduction(PRPPR) score. After the baseline evaluation, the practitioner identifies the interfascial QPI space using high-resolution ultrasonography and then performs the injection using a magnetically guided needle system, administering 1–2 mL of the PDRN pharmacopuncture solution.

The procedure is performed using an in-plane needle approach, enabling real-time visualization of the needle trajectory and tip through ultrasound imaging combined with a magnetic needle-tracking system. Both groups receive the same injection technique and target the same anatomical site; however, the SNG uses a 26G × 60 mm needle, while the LNG uses a 25G × 100 mm needle. All other procedural variables remain consistent across groups.

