#### Statistical analysis

2.6.2

All statistical analyses will be performed using R software (version 4. X. X; R Foundation for Statistical Computing, Vienna, Austria). All tests will be two-tailed, with statistical significance defined as *p* < 0.05. Continuous variables will be summarized as mean ± standard deviation or median with Interquartile Range (IQR), depending on the data distribution. Categorical variables will be presented as frequencies and percentages.

For the primary outcome, changes in NRS scores will be analyzed according to the data distribution. Between-group comparisons will be performed using an independent *t*-test if the normality assumption is satisfied; otherwise, the Wilcoxon rank-sum test will be used. Within-group changes will be assessed using a paired *t*-test or the Wilcoxon signed-rank test, depending on whether the data meet normality assumptions.

For the secondary outcomes, changes in lumbar ROM from baseline will be analyzed using the same statistical methods applied to the primary outcome. Between-group comparisons will be conducted using an independent *t*-test or the Wilcoxon rank-sum test, while within-group comparisons will be analyzed using a paired *t*-test or the Wilcoxon signed-rank test, depending on data normality.

The ODI will be categorized into predefined functional disability levels, and differences in distribution between groups will be analyzed using the Chi-square test or Fisher’s exact test, as appropriate.

PRPPR will be assessed immediately after treatment and again at 24–36 h post-intervention. Between-group comparisons will be conducted using an independent *t*-test or the Wilcoxon rank-sum test, while within-group comparisons will be analyzed using a paired *t*-test or the Wilcoxon signed-rank test, depending on the data characteristics.

In addition, procedural characteristics and usability-related variables associated with needle length—including deep-layer reach success rate, number of insertions, procedure time, and operator usability score—will be summarized using descriptive statistics. When appropriate, exploratory between-group comparisons will be conducted using the Mann–Whitney U test or the Chi-square test. These analyses will serve as supportive reference analyses and will not directly influence the interpretation of the primary clinical outcomes.

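### The 80% power in section 2.6.1 and the patient-level test in section 2.6.2 hold only if outcomes are uncorrelated within clinics, because needle length is fixed by clinic with two clinics per group

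*Protocol article*

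**What the plan says.** Section 2.6.1 sizes the study for a two-sample t-test. It states that "the effect size for this study was set at Cohen’s d = 0.56", works "with a significance level of 0.05 and a statistical power of 80"%, and concludes that "the minimum required sample size was calculated to be 104 participants (52 per group"). It then continues "Allowing for an anticipated dropout rate of approximately 10"% and sets a target of 120, "with 60 allocated to the short-needle group and 60 to the long-needle group". No design effect, ICC or clinic term appears.

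Section 2.1 says that two of the four clinics contribute only short-needle cases and the other two only long-needle cases, and describes this as follows: "This approach represents a site-level data extraction scheme, rather than a randomized allocation process". Section 2.3.2 repeats the arrangement as an inclusion criterion, naming the clinics for each needle.

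Section 2.6.2 compares NRS change between groups with an independent t-test, or a Wilcoxon rank-sum test if normality fails. On sidedness it says "All tests will be two-tailed, with statistical significance defined as" p < 0.05. Its last paragraph allows ANCOVA or regression, but only if baseline differences between the groups are significant, and it does not name clinic as a factor. Section 3 lists selection bias from site-based allocation as a limitation and says nothing about correlation within clinics.

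**The concern.** The sample size formula and the primary test both need each patient to carry independent information about the needle effect. Here every patient in a clinic gets the same needle. Anything that shifts NRS change for a whole clinic (operators, assessors, patient mix) therefore goes straight into the group difference. The protocol itself makes such shifts plausible: section 2.5.2.3 says assessors know the group, and section 3 says the setting reflects varying patient characteristics and an operator learning curve.

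If outcomes are correlated within clinics, two things follow. The power at a genuine 5% level is below the stated 80%. The unadjusted t-test also uses too small a standard error, so its p-values and confidence intervals are too optimistic. The second matters more, because a difference between two pairs of clinics could be reported as a significant effect of needle length.

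**Working it through.** **Inputs from the protocol.** d = 0.56, two-sided alpha 0.05, power 80%, 52 per group, target 60 per group (sections 2.6.1 and 2.6.2); four clinics, two per group (sections 2.1 and 2.3.2).

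**Assumptions, not in the protocol.** ICC of 0.01, 0.05 and 0.10; equal clinic sizes, so m = 60/2 = 30 per clinic with 120 patients, or 52/2 = 26 with 104.

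**Step 1: the stated figure.** With independent patients, exact noncentral-t power at d = 0.56 is 79.97% at 51 per group and 80.7% at 52. The stated 52 per group reproduces. For dropout, 104/0.9 = 115.6, so 116, and the target of 120 covers it.

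**Step 2: power allowing for clinics.** The design effect is DE = 1 + (m − 1) × ICC. The standard error of the group difference, in SD units with n per group, is SE = √(2 × DE/n). Power is Φ(0.56/SE − 1.96), treating the clustered SE as known. For 120 patients at ICC 0.05:
- DE = 1 + 29 × 0.05 = 2.45
- SE = √(2 × 2.45/60) = 0.286
- power = Φ(1.96 − 1.96) = 50%

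**Step 3: a clinic-level test.** A t-test on the four clinic means has the same SE but only 4 − 2 = 2 degrees of freedom, with critical value 4.30. Its power comes from the noncentral t with noncentrality 0.56/SE.

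**Step 4: type I error of the planned t-test.** This was simulated with 20,000 studies per setting and no true needle effect.

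| Patients | ICC | DE | √DE | Power, SE known | Power, clinic-level (2 df) | Type I error, planned t-test |
|---|---|---|---|---|---|---|
| 120 | 0 | 1.00 | 1.00 | 87% | 40% | 5% |
| 120 | 0.01 | 1.29 | 1.14 | 77% | 33% | 9% |
| 120 | 0.05 | 2.45 | 1.57 | 50% | 21% | 21% |
| 120 | 0.10 | 3.90 | 1.97 | 34% | 16% | 33% |
| 104 | 0 | 1.00 | 1.00 | 81% | 36% | 5% |
| 104 | 0.01 | 1.25 | 1.12 | 72% | 31% | 8% |
| 104 | 0.05 | 2.25 | 1.50 | 48% | 20% | 20% |
| 104 | 0.10 | 3.50 | 1.87 | 33% | 15% | 31% |

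The column √DE is roughly the factor by which the planned t-test understates its standard error. It gives a hand check on the simulation: at 120 patients and ICC 0.05, 2 × [1 − Φ(1.96/1.565)] = 21%.

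**Step 5: can more patients at these clinics help?** As n grows with two clinics per group, SE² tends to the ICC. Reaching 80% power needs SE below 0.56/(1.96 + 0.84) = 0.20, so SE² below 0.04. Once the ICC is about 0.04 or more, no number of patients at these four clinics is enough.

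**The case against.** The strongest reply is that the size of the loss rests on an ICC the protocol does not give. That stands. At ICC 0 the 80.7% is correct, so a reader who infers that the calculation is wrong, or that power is certainly well below 80%, goes beyond the documents. What they show is that the figure depends on an unstated condition which the design gives no reason to expect.

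A second reply is that the clustered power figures do not describe the planned test. This also stands. In the same simulations with 120 patients, the unadjusted t-test rejects in about 83%, 76% and 73% of studies at d = 0.56 for ICC 0.01, 0.05 and 0.10. It does so only because it also rejects too often when there is no effect, so this is not power at a 5% level.

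Third, the primary outcome is measured immediately after one procedure, and section 2.3.4 does not count those who complete it as dropouts. Nearly all 120 should have primary data, so the 120-patient rows are the fairer ones. They still fall below 80% at ICC 0.01.

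Fourth, the protocol calls itself preliminary and exploratory (abstract and section 3). A reader might infer that a non-significant result would be taken to show that needle length does not matter, but nothing in the text says so. The exploratory label does not remove the stated 80% power or the p < 0.05 rule.

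The source of the effect size might also be attacked, since section 2.6.1 draws on a different comparison: "In a double-blind randomized controlled trial evaluating pharmacopuncture in patients with chronic LBP, the mean reduction in pain after 3 weeks was 2.74 points" (active arm). However, that section admits that no prior study matches and argues separately that about 1 point is clinically relevant. Little more than wording is left of that criticism.

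Finally, an analysis plan not shown might add a clinic-aware analysis. It would not correct the power and the primary test that this document already states.

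**Conclusion.** Wrong as written. Section 2.6.1 claims a power, and section 2.6.2 names a primary test, that both require independent patients; sections 2.1 and 2.3.2 set up a comparison of two clinics with two clinics. The conditional adjustment in section 2.6.2 does not repair this. It is triggered only by significant baseline differences, and clinic could not enter as a fixed effect in any case because it is aliased with needle group.

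The mechanism is certain; the size is not. Even the smallest ICC examined, 0.01, takes 120 patients below the stated power and raises the type I error to about 8–9%. At 0.05 power is about half and the type I error about one in five. These figures rest on the assumed ICCs and equal clinic sizes, and the power figures in the known-SE column are optimistic for any real test on four clinics.

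**What to change.** In section 2.6.1, state that 80% power holds only if there is no within-clinic correlation, and give the range of power by assumed ICC for the two-versus-two clinic design.

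In section 2.6.2, state that the patient-level p-value and confidence interval ignore clinic clustering, and present the needle comparison as exploratory. Add either a clinic-level or mixed-model analysis with small-sample degrees of freedom (2), or a sensitivity range for the confidence interval over assumed ICCs.

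The cost is a rewording of two sections and one added analysis, with no extra patients. The stated power becomes less favourable and the interval wider.

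Observing both needles within each clinic is an optional redesign, since section 2.1 says all four sites routinely use both. It should not be assumed to preserve 80% power. It would change the clinic-specific inclusion criterion in section 2.3.2 of an approved and registered study. It would also need control for confounding by indication, because section 2.1 says needle choice follows clinical circumstances. Its power depends on balance: with the same overall split in every clinic and no clinic-by-needle variation, Φ(0.56 × √(n₁n₂/120) − 1.96) is about 87% at 60/60, 80% at 84/36 and 76% at 90/30.

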Despite these strengths, this study has several inherent limitations due to its exploratory observational design. First, the site-based allocation approach may introduce selection bias. Second, because the intervention was conducted as a single session with short-term follow-up (24–36 h), the study design does not permit evaluation of sustained or cumulative treatment effects. Third, not all participants underwent imaging-based diagnostic confirmation, which may lead to diagnostic heterogeneity and should be taken into account when interpreting the findings.

Future research should include randomized controlled trials to verify the independent effects of needle length and NGS application, as well as quantitative imaging-based assessments of needle tip visibility and tracking accuracy. Additionally, studies incorporating repeated interventions, long-term follow-up, and subgroup analyses based on BMI, muscle thickness, or pain phenotype may further clarify patient-specific treatment responses. Finally, cost-effectiveness analyses would help determine the practical value of ultrasound-guided interfascial pharmacopuncture in primary care settings and contribute to establishing clearer clinical indications and standardized application criteria for the QPI-guided approach.

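### The 80% power and the 104-patient minimum treat patients as independent although needle length is fixed for four whole clinics, so power and the 5% level hold only if clinics hardly differ

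*Protocol article*

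**What the plan says.** The sample size in section 2.6.1 rests on one comparison of independent patients. There "the effect size for this study was set at Cohen’s d = 0.56", a two-sample t-test is applied "with a significance level of 0.05 and a statistical power of 80" per cent, and "the minimum required sample size was calculated to be 104 participants (52 per group"). The only later adjustment is for about 10% dropout, which leads to a target of 120, 60 per needle.

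Section 2.1 sets the needle by clinic: "two sites will be designated to contribute only cases treated with short needles", and the other two contribute only long-needle cases. The inclusion criteria in 2.3.2 repeat this, naming each clinic with its needle.

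Section 2.6.2 states that "All tests will be two-tailed" at p < 0.05. For the primary outcome, "Between-group comparisons will be performed using an independent" t-test, or a Wilcoxon rank-sum test if normality fails. Neither has a clinic term. Regression adjustment is foreseen only for variables that turn out to differ at baseline. The limitations in section 3 say that "the site-based allocation approach may introduce selection bias". They do not mention clustering or its effect on power.

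**The concern.** All patients of a clinic receive the same needle length. Anything that shifts a clinic's mean NRS change, such as the operator, the unblinded assessor or the mix of patients, therefore shifts the needle comparison too. Its variance has a between-clinic part that neither the sample size formula nor the planned test contains, and only two clinics per needle inform it.

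This is a fault in precision and error rate as well as a question of selection. It would remain if clinics had been assigned to needles at random. At stake is the reading of the primary result: a p-value below 0.05 could reflect ordinary differences between clinics, and a null result could be taken as adequately powered when it was not. The abstract expects the results to contribute to standard criteria for choosing a needle.

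**Working it through.** **Inputs from the article.** d = 0.56, two-sided alpha 0.05, power 80%, 52 or 60 per group, about 10% dropout, four clinics with two per needle. The cited trial's reductions of 2.74 and 1.76 points differ by 0.98, so the implied SD is 0.98/0.56 = 1.75 points.

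**Assumptions.** Equal clinic sizes: m = 26, 27 or 30 per clinic for 104, 108 (120 less 10%) or 120 evaluable patients. The article gives no ICC; the range 0 to 0.10 is assumed.

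**1. The stated figure.** The normal approximation gives 2 × (1.960 + 0.842)² / 0.56² = 50.1, so 51 per group. The exact noncentral-t solution is 51.03, so 52 per group and 104 in total. Exact power under independence is 80.7% (104), 82.2% (108) and 86.0% (120). The 104 reproduces.

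**2. Power with clustering, patient-level degrees of freedom.** Design effect DE = 1 + (m − 1) × ICC; noncentrality = 0.56 × √(n / (2 × DE)), with n per group. For example, at 104 patients and ICC 0.01, DE = 1 + 25 × 0.01 = 1.25, noncentrality = 0.56 × √(52/2.5) = 2.55, power 71.6%.

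**3. Power of a test on the four clinic means.** Noncentrality = 0.56 / √(ICC + (1 − ICC)/m), with 2 degrees of freedom. At ICC 0 and m = 30 this is 0.56 × √30 = 3.07, and power is 39.9%.

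**4. Type I error of the planned t-test.** Approximately 2 × [1 − Φ(1.96/√DE)], checked by simulation with 20,000 runs per setting.

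| Assumed ICC | Between-clinic SD (points) | Power, 104, patient-level df | Power, 120, patient-level df | Power, 104, 2 df | Power, 120, 2 df | Type I error, m = 30: formula (simulated) |
|---|---|---|---|---|---|---|
| 0 | 0 | 80.7% | 86.0% | 36.2% | 39.9% | 5.0% (4.9%) |
| 0.01 | 0.18 | 71.6% | 76.4% | 30.9% | 33.4% | 8.4% (8.5%) |
| 0.02 | 0.25 | 63.7% | 67.7% | 27.1% | 28.9% | 11.9% (11.8%) |
| 0.05 | 0.39 | 47.0% | 49.4% | 20.4% | 21.2% | 21.0% (21.8%) |
| 0.10 | 0.55 | 32.7% | 33.8% | 15.2% | 15.5% | 32.1% (33.0%) |

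The between-clinic SD is 1.75 × √ICC.

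**5. How much clinic variation 80% power tolerates.** With patient-level degrees of freedom, the largest ICC is 0.0008 at 104 patients, 0.0023 at 108 and 0.0062 at 120. These are between-clinic SDs of about 0.05, 0.08 and 0.14 NRS points.

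**6. More patients do not solve it.** With two clinics per needle and ICC 0.05, unlimited patients per clinic give a noncentrality of 0.56/√0.05 = 2.50. Power then stops at Φ(2.50 − 1.96) = 71% by the normal approximation, and at 30% on 2 degrees of freedom.

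**7. The planned test's rejection rate.** At 104 patients, the unadjusted t-test still rejects in 78% (ICC 0.01) or 73% (ICC 0.05) of simulated trials with d = 0.56. Its type I error is then 8% or 20%, so this is not power at the 5% level.

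**The case against.** **The size is driven by an assumption.** This is true: every figure away from ICC 0 depends on an ICC that the article does not give. Sections 2.1, 2.4 and 2.5.2.3 describe one technique, one device, one agent, uniform assessor training and predefined outcome definitions, all of which should reduce clinic differences. They do not show that the differences vanish. Section 3 itself expects the real-world setting to bring varying patients and operator learning curves, and 2.5.2.3 says that assessors are unblinded.

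**The four clinics are fixed and named.** If inference is only about these four, clinic differences are confounding rather than sampling variance, and section 3 already concedes selection bias. This is a fair alternative view, and the power figures above belong to the view that clinics are a sample of possible clinics. Under the fixed view, however, the same differences bias the contrast and the p-value does not reflect them.

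**The study calls itself preliminary and exploratory.** It does, but 2.6.1 still claims 80% power and 2.6.2 still tests the primary outcome at 5%.

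**A stronger reading is tempting:** that the stated power is lost unless clinics do not differ at all. The figures do not support this. With all 120 patients evaluable, 80% survives to an ICC of about 0.006, and the 104 minimum has a sliver of slack. Nor can a reader infer that 104 was miscalculated, since it reproduces.

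**The analysis plan may add a clinic term.** The power claim and the primary test are stated here, against a design stated here. A fixed clinic effect cannot be added, because clinic determines needle, and a random clinic intercept is poorly estimated from four clinics.

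**Conclusion.** The point holds in this form: the stated power and the 5% level of the planned t-test require between-clinic variation in mean NRS change to be practically nil. Section 2.6.1 does not state that condition. An assumed between-clinic SD of 0.18 points (ICC 0.01) already lowers power to 72% with 104 patients and 76% with 120. An SD of 0.39 points (ICC 0.05) lowers it to 47% and 49%, with about 21% false positives from the planned test at 30 per clinic. These powers credit patient-level degrees of freedom, which four clinics do not truly supply. On clinic means, power is 36% (104) or 40% (120) even with no clinic variation.

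The conclusion rests on equal clinic sizes, an SD of 1.75 points, the assumed ICC range, and clinics viewed as a sample. The documents do not show which ICC applies, so no single figure for the loss can be claimed. The direction and the missing condition do not depend on it.

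**What to change.** No extra patients or clinics are needed.

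- **2.6.1:** State that 80% (104 patients), 82% (108) and 86% (120) are the power of the patient-level t-test assuming no between-clinic variation. Tabulate power at ICC 0 to 0.10, marking the ICC as assumed. Give the power of the clinic-level analysis separately, because its 36% to 40% at ICC 0 differs from the patient-level figures.
- **2.6.2:** Report the needle difference with a 95% interval from one named clinic-level analysis, the four clinic means on 2 degrees of freedom. Label the patient-level t-test or Wilcoxon p-value as descriptive or exploratory.
- **Section 3:** Name clustering by clinic, with its effect on power and type I error, beside selection bias.

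The cost is a few sentences, one table and one simple analysis. The downside is a less favourable stated power and a wider interval. Section 2.1 reports that nobody had been recruited at submission, so the change can still be made before any outcome is seen if that remains true.
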